# CyFiT telehealth: protocol for a randomised controlled trial of an online outpatient physiotherapy service for children with cystic fibrosis

**DOI:** 10.1186/s12890-019-0784-z

**Published:** 2019-01-24

**Keywords:** Cystic fibrosis, Telehealth, Telemonitoring, Children, Health economics, Physical activity

## Abstract

**Background:**

Telehealth and telemonitoring is an emerging area of study in people with cystic fibrosis (CF), with the potential of increasing access to care, and minimising infection control risks to patients without compromising their health outcomes. To date, limited evidence is available to support the use of telehealth in paediatric population with CF in a clinical setting. This study aims to investigate the utility of a multimodal telehealth-based outpatient physiotherapy service and assess its effect on quality of life, functional exercise capacity, hospital admission and intravenous antibiotic requirements, lung function, processes of care, participation in activities of daily living, and health economics associated with operating an innovative service.

**Method:**

This single centre, prospective, parallel, randomised, controlled, non-inferiority trial aims to recruit 110 children with CF between the ages 8 to 18 years of age. Participants will be randomised to the Usual Outpatient Physiotherapy Service group (Usual OPS) or the telehealth intervention group (CyFiT OPS). Quality of life, participation in activity of daily living, functional exercise capacity and patient perception of care will be examined every six months using the Cystic Fibrosis Questionnaire-Revised (CFQ-R), Children’s Assessment of Participation and Enjoyment (CAPE), Preferences for Activities of Children (PAC) questionnaire, Modified Shuttle Test-25 (MST25), and Measure of Process of Care (MPOC-20) questionnaire. Physiological measurements collected during routine clinical visits such as spirometry, body weight and height, information will be retrospectively retrieved via a chart review at the end of the study.

**Discussion:**

We anticipate that this multi-modal telehealth service will deliver a comparable service to traditional face-to-face models. An alternative to existing outpatient physiotherapy services may potentially increase patient options for access to care and patient-orientated outcomes such as quality of life. If deemed appropriate, the new model of care can be integrated into clinical practice immediately.

**Trial registration:**

This trial is registered with the Australian and New Zealand Clinical Trial Registry (ACTRN12617001035314) last updated 17th July 2018.

**Electronic supplementary material:**

The online version of this article (10.1186/s12890-019-0784-z) contains supplementary material, which is available to authorized users.

## Background

Cystic fibrosis (CF) is an inherited disorder of exocrine function that affects the lungs, digestion, and multiple other body systems. Ongoing physiotherapy in the form of airway clearance techniques and exercise therapy is integral to the management of CF [1]. Adherence to long-term physiotherapy regimens, however, can be difficult at home [2–4]. Poor adherence can lead to more frequent visits to hospital, which potentially increases exposure to harmful infections at the hospital, as well as time away from school and work. At our clinic, physiotherapists utilise outpatient physiotherapy services (OPS) in addition to regular physiotherapy reviews during multidisciplinary (MDT) clinics to encourage prescribed physical activity and effective airway clearance techniques [1]. Traditionally, OPS are delivered via face-to-face consultations in a hospital setting. An alternative mode of delivering OPS is therefore needed to enable better access to healthcare and minimise risk of cross infection. This study aims to investigate the efficacy of an innovative telehealth-based outpatient physiotherapy service for children with CF.

Telehealth in the form of real-time videoconferencing enables patients to access health care from virtually anywhere. The risk of cross infection may be reduced as patients are not required to visit hospital as frequently. Other forms of telehealth may improve patient experiences and better clinical outcomes in ways that were previously not possible. For example, virtual group exercise may offer much needed peer-driven social/psychological support between patients as children are currently unable to physically interact with other children with CF due to infection precautions [1]. In addition, smartphone and wearable technologies may assist physiotherapists in clinical decision making as they are able to access a large amount of health-related data remotely [5].

To date, the role of telehealth in the physiotherapy management of CF is unclear, although various centres internationally are experimenting with different types of telehealth interventions. Telehealth in the form of telemonitoring via spirometry have previously been investigated [6–8]. More recent publications have suggested the use of telehealth to increase access to health care (Jamie [9]), as well as encouraging physical activity [10], and mobile-based applications ([11]; J. [12]) in adults with CF. Limited research is available for children with CF.

We aim to investigate the efficacy of various modes of telehealth at our clinic. In this trial, we have developed a multi-modal telehealth-based OPS specific for children with CF. This trial seeks to answer the following question: Can CyFiT OPS offer a non-inferior health outcome and quality of life compared to Usual OPS for children with CF? If proven to be effective, the new model of healthcare delivery will be integrated into our existing services as an alternative option for families particularly those living far away from the hospital CF Centre.

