## Methods/design

### Study aim

The aim of this study is to investigate the efficacy of a telehealth outpatient physiotherapy service (CyFiT OPS) on patient quality of life, clinical efficacy and cost-effectiveness of healthcare delivery when compared to Usual OPS.

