### Study design

This is a single centre, prospective parallel randomised controlled non-inferiority trial with a 1:1 allocation across two treatment arms: Usual OPS and CyFiT OPS. Children receiving Usual OPS will serve as the control group for the trial.

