#### Primary outcome measure

##### Cystic fibrosis questionnaire – Revised (CFQ-R)

The CFQ-R is a valid and reliable quality of life measure for children with CF from 6 years of age (A. L. [18]). The score is positively correlated with pulmonary function in adolescents with CF [19]. It includes nine quality of life domains: physical (8 items), role limitation, vitality (5 items), emotional (5 items), social (6 items), body image (3 items), eating disturbances (3 items), treatment burden (3 items), and health perceptions (3 items); as well as three symptom-based scales: weight (1 item), respiratory (6 items), digestion (3 items). All items are scored on a 4-point Likert Scale (1 = Very true/Always to 4 = Not at all true/Never). Scores for each domain will be analysed individually.

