### Blinding

The nature of this trial prevents the blinding of both the treating clinicians and patients. Both clinicians and patients will be exposed to the allocation via a) what modality they receive their physiotherapy service, and b) health-related data from activity trackers. Outcome measures will be collected by a blinded assessor. Randomisation will only occur after initial baseline assessment. Patients will always be approached by an unblinded clinical team prior to reassessment to mitigate risk of unblinding of the assessor (e.g. removing wristbands for the assessment).

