### Sample size

The minimum clinically important difference (MCID) for the CFQ-R has been previously calculated for people with CF who are medically stable (using distribution/Smallest Error Measurement method) as 6.1 (A. L. [24]). Standard deviation on CFQ-R improvement (treatment burden) has been previously reported as 8.6 [25]. A power of 0.9 and an alpha value of 0.025 has been chosen for this trial. Using this information, sample size for each group has been calculated to be 42 participants per group [26]. To allow for patient dropout, a total of 55 participants per group will be recruited.

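### The trial question covers health outcome as well as quality of life, but only the CFQ-R is primary and sized, so the plan cannot support non-inferiority on a clinical outcome

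*Protocol article*

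**What the plan says.** The last paragraph of the Background in the Protocol article puts the trial question as "Can CyFiT OPS offer a non-inferior health outcome and quality of life compared to Usual OPS for children with CF". The Study aim likewise separates the clinical side from quality of life: the service is to be judged "on patient quality of life, clinical efficacy and cost-effectiveness of healthcare delivery when compared to Usual OPS". The Study design section calls the trial a "single centre, prospective parallel randomised controlled non-inferiority trial with a 1:1 allocation across two treatment arms".

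The only primary outcome is the CFQ-R, introduced with "The CFQ-R is a valid and reliable quality of life measure for children with CF from 6 years of age". Each of its domains is to be analysed individually. The MST25 and the chart-review items (hospital use, intravenous antibiotic days, spirometry) are listed as secondary outcomes.

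The Sample size section works only from CFQ-R figures (MCID 6.1, SD 8.6 for treatment burden, power 0.9, alpha 0.025) and reports that "sample size for each group has been calculated to be 42 participants per group", with 55 per group recruited to allow for dropout.

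The Data analysis section describes generalised linear models that look for differences between the arms, with significance at p < 0.05. On blinding: "The nature of this trial prevents the blinding of both the treating clinicians and patients". The outcome assessor is blinded.

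On use of the result, the Background says the service will become an alternative option within existing services if shown to be effective. The abstract's Discussion says that, if judged appropriate, "the new model of care can be integrated into clinical practice immediately".

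**The concern.** The question needs two answers, and the plan is built to give one. No clinical measure is named as the health outcome that has to be non-inferior, and none has a margin or a sample size. Under the analysis as described, the only available support for the health-outcome half would be the absence of a significant difference on an unsized secondary outcome. In a non-inferiority trial that is the wrong inference, because a small or noisy comparison tends to be non-significant whether or not there is a loss.

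The CFQ-R cannot carry both halves. Its respondents know their allocation, and one arm receives an activity tracker and a new telehealth platform. A blinded assessor does not remove bias from an unblinded respondent. A child could report stable quality of life while exercise capacity or lung function falls.

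The choice of question, primary outcome and sizing basis is made in this document, so the mismatch is not a detail that a later analysis plan would normally settle.

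**Working it through.** **1. The plan's own figure.** Inputs from Sample size: difference 6.1, SD 8.6, power 0.9, alpha 0.025. Sidedness is not stated; it is taken here as one-sided, with a true difference of 0.

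n per group = 2 × (1.96 + 1.2816)² × 8.6² / 6.1² = 2 × 10.508 × 73.96 / 37.21 = 41.8, so 42.

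This matches the plan. Reading alpha as two-sided 0.025 would give 50. The implied dropout is 1 − 42/55 = 23.6%. The stated number is therefore correct arithmetic, for one CFQ-R scale.

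**2. What that size gives for any continuous clinical measure, in SD units.** No clinical SD is needed for this step.

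- 95% half-width = 1.96 × √(2/n). At n = 42: 1.96 × 0.2182 = 0.43 SD. At n = 55: 1.96 × 0.1907 = 0.37 SD.
- Smallest margin with 90% power (one-sided 0.025, true difference 0) = 3.2416 × √(2/n). At n = 42: 0.71 SD. At n = 55: 0.62 SD.

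**3. Illustration on a clinical scale.** The documents give no SD or margin for FEV1. Assumed: SD of 12-month change of 8, 10 or 15 points of % predicted, and a single unadjusted comparison. SE = SD × √(2/n), and the chance of a non-significant result for a true loss d is 1 − [Φ(d/SE − 1.96) + Φ(−d/SE − 1.96)].

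| Assumed SD | 8 | 10 | 15 |
|---|---|---|---|
| 95% half-width, n = 42 | 3.4 | 4.3 | 6.4 |
| True 5-point loss non-significant, n = 42 | 18% | 37% | 67% |
| True 5-point loss non-significant, n = 55 | 9% | 25% | 58% |
| True 3-point loss non-significant, n = 42 | 60% | 72% | 85% |

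**4. What adding a clinical non-inferiority test would cost in power.** If its margin were also about 0.71 SD, so that it too had 90% power, joint power at 42 per group would be 0.9 × 0.9 = 81%, assuming independence. With a 5-point FEV1 margin and the same SDs, power for that test alone is 82%, 63% or 33%, and joint power is about 74%, 57% or 30%. Reaching 90% for a 5-point margin alone would take 54, 85 or 190 per group.

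**The case against.** A reader might infer that CyFiT would be adopted on the CFQ-R alone, whatever the clinical results. The documents do not support that. No formal adoption rule is stated. The abstract makes integration conditional on the service being judged appropriate, and the Background makes it conditional on effectiveness, directly after a question that names health outcome. Adoption is also only as an alternative option. A visible clinical loss could count against it.

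A reader might also infer that the CFQ-R says nothing about health, or that CFQ-R non-inferiority would be declared about 90% of the time if the arms were equal. The first goes too far: the instrument has physical, health-perception and respiratory scales, and the protocol reports a positive correlation with pulmonary function in adolescents. What it lacks is an objective measure. The second holds only for one scale with the treatment-burden SD of 8.6. Domains are analysed individually, and no other SD is given.

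It is also fair to say that one patient-reported primary with objective secondaries is an ordinary design, and that open-label reporting is unavoidable here and disclosed. Both arms keep three-monthly face-to-face reviews. Clinical outcomes are collected and compared, so a large loss could be seen. Repeated-measures models and up to 55 per group would narrow the intervals somewhat.

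All of this limits the point but does not remove it. None of it turns a test for differences on an unsized secondary into evidence of non-inferiority, and the question as worded claims that evidence.

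**Conclusion.** The point holds as a mismatch between the question and what the trial can show. The sample size is correctly calculated and serves the quality-of-life half only. For a continuous clinical outcome, the trial can reliably exclude only losses of about 0.7 SD or more at 42 per group, or about 0.6 SD at 55. Those figures rest on a two-group comparison of means at one-sided 0.025 with no true difference, and need no clinical SD. The FEV1 percentages are illustrations on assumed SDs and are not properties of this trial.

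The documents do not show that a clinical loss would be ignored in the adoption decision. They do show that a claim of non-inferior health outcome would have no adequate basis under the analysis described. The point is worth correcting because it changes what the trial may conclude.

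**What to change.** **Main change.** Limit the non-inferiority question in the Background, and the conclusion drawn from it, to quality of life on the CFQ-R. Report between-group 95% confidence intervals for 12-month MST25 distance and FEV1 beside the CFQ-R result, and state that a non-significant difference on either is not evidence of non-inferiority. This needs wording only, with no new data, visits or patients. The price is a narrower headline claim.

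**Only if a clinical margin can be justified before unblinding.** Add one clinical outcome as a key secondary, tested in fixed sequence after the CFQ-R at the same alpha, and require both confidence limits to clear their margins before the two-part claim is made. MST25 distance is the cleaner choice, because the blinded assessor takes it, whereas follow-up spirometry comes from chart review. CFQ-R power is unaffected. Joint power is about 81% only for a clinical margin near 0.71 SD (independence assumed), and lower for a tighter one. The sponsor should state the power for the chosen margin. If it is too low to be useful, the main change is the better course.

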## Methods/design

### Study aim

The aim of this study is to investigate the efficacy of a telehealth outpatient physiotherapy service (CyFiT OPS) on patient quality of life, clinical efficacy and cost-effectiveness of healthcare delivery when compared to Usual OPS.

### Study design

This is a single centre, prospective parallel randomised controlled non-inferiority trial with a 1:1 allocation across two treatment arms: Usual OPS and CyFiT OPS. Children receiving Usual OPS will serve as the control group for the trial.

### Study setting

All trial activities will be conducted through the Children’s Health Queensland Hospital and Health Service (CHQ-HHS) CF service in Queensland Australia. The CF service operates from Lady Cilento Children’s Hospital (LCCH), South Brisbane, Queensland, Australia and outreach service locations in Queensland.

### Participants

#### Inclusion criteria

Participants will be children (i) with a confirmed medical diagnosis of CF, (ii) aged between eight to eighteen years (inclusive), (iii) who have access to the internet in their local area (e.g. at home, a local health centre, or the home of a family-selected relative or friend), (iv) through a device which enables videoconferencing (e.g. personal computer, tablet, or phones).

#### Exclusion criteria

Children will be excluded from this study if they present with (i) an acute or chronic medical co-morbidity that would prevent or significantly limit participation in the study, or (ii) behavioural or intellectual difficulties that would prevent full participation in face-to-face physiotherapy assessment, or physiotherapy intervention via telehealth, or (iii) they are involved in another study that precludes enrolment in any other study.

### Recruitment process

Participants of this study will be recruited from the CHQ-HHS CF service, Queensland, Australia. This service is provided via inpatient and outpatient services at (i) the CHQ-HHS LCCH, (ii) regional Queensland Health hospitals.

Children will be identified by the study coordinator who is a senior physiotherapist will review each patient attending the CF clinic, OPS, or hospital ward daily. The inclusion and exclusion criteria will be used to determine the eligibility for each child. All eligible children will be approached by the treating physiotherapist. If families express interest in the trial, a member of the research team will provide written information and seek consent/assent as appropriate. If the parents agree for their child to proceed with the study, informed written consent will be gained from the parent and assent from the child.

Once informed written consent is gained, baseline assessment will be collected by the blinded research assessor, which includes seven elements, the:, (i) Cystic Fibrosis Questionnaire-Revised (CFQ-R) (A. [13]), (ii) Modified Shuttle Test (MST25) [14], (iii) Measure of Processes of Care (MPOC) Questionnaire (S. M. [15]), (iv) Children’s Assessment of Participation and Enjoyment (CAPE), (v) Preferences for Activities of Children (PAC) (G. A. [16]), (vi) lung function (i.e. FEV_1_, FVC, FEV_1_/FVC, FEF_25–75%_)[17], and (vii) anthropometric data: height (cm), weight (kg) and age (y).

Once baseline assessment has been scheduled, a physiotherapist will randomise the child to one of the two treatment arms by opening a sealed allocation envelope in front of the child. The physiotherapist will then discuss with the families the requirements relevant to their allocation (e.g. how to access the telehealth system).

### Randomisation

Children will be randomised via concealed random allocation. A computerised random number sequence will be generated that corresponds to the two study arms (1 = Usual OPS, 2 = CyFiT OPS) in balanced-blocks of eight participants (i.e. 4 Usual OPS, 4 CyFiT OPS). The result of each randomisation will be concealed inside a sequentially numbered, opaque envelope. Intervention will be provided to each child in one of two treatment arms: Usual OPS or CyFiT OPS. The allocation of each child will be recorded on an electronic, password protected spreadsheet that is unknown to the trial assessor, and then contents of the envelope will be discarded.

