***Outpatient physiotherapy services (OPS)***
**:**
Apart from these routine check-ups, OPS may be clinically indicated on an individual patient basis. Timing and frequency of OPS will be determined by the child’s treating physiotherapist according to clinical indicators which will be identical for children in both treatment arms. If OPS is required, it will be delivered in a mode according to the group that the child has been randomised to - Usual OPS or CyFiT OPS. Physiotherapy in both arms will be delivered by the same physiotherapy team. Only the mode of delivering OPS will differ according to group allocation (face-to-face or telehealth).

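### A constant block of eight in an unblinded single-centre trial leaves about 19% of allocations foreseeable, and the opened slips are thrown away: a cheap improvement

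*Protocol article*

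**What the plan says.** All of this is in the protocol article.

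- **Sequence.** Under Randomisation, "A computerised random number sequence will be generated that corresponds to the two study arms", "in balanced-blocks of eight participants (i.e. 4 Usual OPS, 4 CyFiT OPS"). One block size is given, and no stratification is described. Study design gives a single centre and 1:1 allocation.
- **Concealment.** Each result is "concealed inside a sequentially numbered, opaque envelope" (Randomisation). Recruitment process adds that the envelope is sealed.
- **Who acts.** In Recruitment process, a study coordinator who is a senior physiotherapist screens patients daily. Then "All eligible children will be approached by the treating physiotherapist", and a member of the research team gives the written information and seeks consent. Afterwards "a physiotherapist will randomise the child to one of the two treatment arms by opening a sealed allocation envelope in front of the child".
- **Who can see allocations.** "Physiotherapy in both arms will be delivered by the same physiotherapy team" (Outpatient physiotherapy services). "The nature of this trial prevents the blinding of both the treating clinicians and patients" (Blinding).
- **Record.** The allocation goes onto a password-protected spreadsheet hidden from the assessor, and "then contents of the envelope will be discarded" (Randomisation).
- **Timing.** Recruitment process places randomisation after the baseline assessment has been scheduled. Blinding places it only after the baseline assessment itself.

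**The concern.** A constant block is self-revealing. Once four children in a block have gone to one arm, every remaining place belongs to the other. The professional group that makes the first approach also treats both arms openly, so it is well placed to keep a running tally. Opaque envelopes do not protect against deduction from earlier allocations.

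At stake is the comparability of the arms. Someone who can foresee the next arm could bring an approach forward or put it off. Children attend the multidisciplinary clinic about every three months, so a postponed approach is easily made later. If the timing follows features related to quality of life, the arms differ before treatment starts, and later analysis cannot fully remove this. In a non-inferiority trial with a self-reported primary outcome, a tilt towards CyFiT would work in favour of the conclusion the trial hopes to reach.

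The discarded slips are a separate, smaller matter. The slip is the primary evidence of which envelope went to which child, and without it a transcription error in the spreadsheet is harder to trace.

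**Working it through.** **Inputs.** Block of 8, four per arm (Randomisation). Total 110, i.e. 55 per group (Sample size). The Randomisation section gives no predictability figure to reproduce. Assumed, not stated: one envelope series, and an observer who knows the block size and every earlier allocation in the block.

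**Allocations known with certainty, by position.** There are C(8,4) = 70 equally likely orderings. Position k is certain when one arm was used up by position k − 1, with probability 2·C(k − 1, 4)/70:

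| Position | Orderings | Probability |
|---|---|---|
| 1 to 4 | 0 | 0% |
| 5 | 2 | 2.9% |
| 6 | 10 | 14.3% |
| 7 | 30 | 42.9% |
| 8 | 70 | 100% |

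Sum: (2 + 10 + 30 + 70)/70 = 112/70 = 1.6 of 8, or 20%. The closed form 2m/(m + 1) with m = 4 gives the same 8/5 = 1.6.

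**Over the trial.** 110 = 13 × 8 + 6. Full blocks give 13 × 1.6 = 20.8. The last six places add 2/70 + 10/70 = 0.17. Total 20.97, about 21 of 110 (19.1%).

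**Best guess.** Always guessing the arm with more places left gives m + (2^(2m)/C(2m,m) − 1)/2 = 4 + (256/70 − 1)/2 = 5.33 of 8, or 66.6%, against 50% by chance. Over 110 children this is about 73 correct (66.3%).

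**Alternatives.** These were simulated over 110 children with sizes drawn at random. The observer knows the set of sizes but not their order.

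| Block sizes | Certain | Best guess correct |
|---|---|---|
| Fixed 8 | 19% | 66.3% |
| 4, 6, 8 | about 2.3% | 67.9% |
| 6, 8, 10 | about 1.6% | 66.3% |

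Varying the size nearly removes certainty. It does not reduce average guessing.

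**What it could do to the result (illustration).** Assume every foreseeable place is used for steering, and that the children steered to the two arms differ by 0.5 to 1 SD. The documents give neither assumption. With the SD of 8.6 from Sample size, that is 4.3 to 8.6 points. The bias is 0.19 × 4.3 = 0.8 to 0.19 × 8.6 = 1.6 points, or 13% to 27% of the 6.1-point MCID used for the sample size. Partial steering would give proportionately less.

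**The case against.** The other side has a good deal to say.

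- **Safeguards are stated.** The envelopes are sealed, opaque and sequentially numbered. Screening is daily and against criteria, all eligible children are to be approached, and a research-team member seeks consent. The Discussion describes the research team as blinded and outside clinical management. This limits discretion over whether a child is approached. It does not fix when.
- **Staff knowledge is inferred.** No section says that treating physiotherapists know the block size or every earlier allocation, or that there is one envelope series. Recruitment also runs through regional hospitals, so one clinician may not see the full order. This stands, and makes the 19% conditional.
- **Eight is not a small block.** A fixed block of four would leave 33% certain. True, but 19% can still be reduced cheaply.
- **The motive is limited.** Usual OPS may itself include videoconferencing, so a distant family is not denied telehealth in the control arm. This weakens the most obvious reason for steering.

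Two stronger readings are tempting, and the document supports neither. A reader might infer that concealment fails. It does not: about four in five allocations are never certain, including the first four of every block. A reader might also infer that the sequence cannot be audited. But the list is computer-generated, the envelopes are numbered and each allocation is recorded before the slip goes, so the spreadsheet can be checked against the list if it is kept. The article does not say whether it is, and a condensed article's silence on that is no fault.

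Nor should the best-guess rate of about 67% be charged to the constant block size, since varied sizes do no better.

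**Conclusion.** The point holds as a cheap improvement, not as a failure of the randomisation. About 21 of 110 allocations (19%) are foreseeable with certainty to someone who knows the block size and tracks a single envelope series. The article shows the opportunity: an unblinded team in both arms, a treating physiotherapist making the first approach, and one stated block size. It does not show that anyone has the knowledge or would use it. The resulting risk of selection bias is modest and acts through the timing of the approach.

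Discarding the slips loses a source document for no stated benefit, but leaves the comparison with the generated list open.

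The timing contradiction stands on the text alone and needs no assumption: scheduling a baseline assessment and completing it are different events. Under the Recruitment process wording a child could know the arm before answering the baseline quality-of-life questionnaire.

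**What to change.** 1. Draw block sizes at random and keep them from the treating team. Sizes 6, 8 and 10 leave about 1.6% of allocations certain; 4, 6 and 8 leave about 2.3%. If recruitment has begun, change over at the end of the current block.
2. Replace the instruction to discard the contents: keep each opened slip, signed and dated, in the trial file.
3. Reconcile Recruitment process with Blinding so that both say the envelope is opened after baseline assessment is completed.

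**Cost.** The remaining list is regenerated and its envelopes reprinted. The possible imbalance at the end grows slightly. With fixed eights, 110 children stop at the sixth place of a block, so the arms differ by at most 4 − 2 = 2. With blocks of up to ten the difference could reach 5. Against 55 per group this is negligible.

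**Limit.** The average best-guess rate stays at about 66% to 68%. Varied sizes remove near-certain prediction, not informed guessing.
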